#### Day 28 after the QD

We will use the same questions as in the pilot phase-only Day 7 follow-up but will ask about the previous 28 (not 7) days, and we will ask the intervention group about BMN components (eg, texts and website). Participants who do not provide information on smoking status or NRT use by app or questionnaire methods will be sent a text about NRT use since the QD and asked to reply directly.

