#### Follow-up

After baseline, apart from data collection by app and routine sources, the primary data collection mode is by online questionnaires, with links texted or emailed to participants. If there is no response, a reminder text and/or email will be sent first, then participants will be called and hard copy questionnaires with reply paid envelopes will be posted as a final option.

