#### 36 weeks of gestation or delivery (if earlier)

We will ask participants about smoking, adherence to NRT since 28-day follow-up and use of NHS stop smoking support. We will send non-responders a direct-reply text message asking about smoking in the previous 7 days.

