#### Secondary outcomes

Reported smoking abstinence at *both* 28 days and in late pregnancy or at childbirth, with and without appropriate biochemical validation in late pregnancy.Reported smoking abstinence for 24 hours and 7 days at 28 days.Reported number of days NRT is used in the first 28 days following a QD.Reported mean daily nicotine dose in the first 7 days of quitting (‘intensity’ of NRT use).Engagement with BMN intervention components.

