#### Procedures for missing, unused and spurious data

We will assume that participants with missing smoking status are smoking, in line with the Russell standard, meaning people who do not provide data are assumed to be smoking.^39^ Similarly, participants not providing a NRT usage response(s) will be assumed to be not using NRT in the corresponding period. We will investigate the sensitivity of results from the main analyses to departures from these strict missing not at random (MNAR) assumptions, by imputing these missing data under a range of missing at random (MAR) and MNAR scenarios.

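### The Day 28 last-resort text is sent when smoking status is missing but is described as asking about NRT use, so a woman who answers it is still coded as smoking in four secondary outcomes

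*Protocol article*

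**What the plan says.** All references are to the protocol article.

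- **Day 28 after the QD.** The last step for women without data reads: "Participants who do not provide information on smoking status or NRT use by app or questionnaire methods will be sent a text about NRT use" (from the quit date onward), to be answered by return text.
- **36 weeks of gestation or delivery (if earlier).** The corresponding step reads: "We will send non-responders a direct-reply text message asking about smoking in the previous 7 days".
- **Follow-up.** Before any such text, questionnaire non-response is chased in stages: "a reminder text and/or email will be sent first, then participants will be called and hard copy questionnaires" are posted.
- **Daily NicUse recording of behaviours.** Smoking is also recorded each day in the app, and one or two missed days can be filled in later.
- **Secondary outcomes.** Two outcomes rest on Day 28 status alone: "Reported smoking abstinence for 24 hours and 7 days at 28 days". Two more require abstinence at both "28 days and in late pregnancy or at childbirth, with and without appropriate biochemical validation in late pregnancy".
- **Procedures for missing, unused and spurious data.** "We will assume that participants with missing smoking status are smoking, in line with the Russell standard". Sensitivity to this rule will be examined "by imputing these missing data under a range of missing at random (MAR) and MNAR scenarios".

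**The concern.** A rescue contact should collect the item whose absence triggered it. At Day 28, absent smoking status is a named trigger, but the described content of the message is NRT use. A woman who has stopped smoking and replies has given the trial its last chance to learn her status, and on this description the question is not put to her. The missing-equals-smoking rule then makes her a smoker.

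What is at stake is avoidable misclassification, always in the direction of non-abstinence, in four secondary outcomes. The combined outcome shows it most clearly: a woman could have biochemically validated abstinence in late pregnancy and still fail because Day 28 was never ascertained.

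**Working it through.** **The passages side by side**

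| Step | Day 28 | 36 weeks |
|---|---|---|
| Trigger for the text | No smoking status or NRT use from app or questionnaire | Non-response |
| Stated content | NRT use since the quit date | Smoking in the previous 7 days |
| Other source of smoking status | None described once app and questionnaire have failed | NHS records from week 36 |
| If status is still missing | Coded as smoking | Coded as smoking |

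The chain is: status missing after app, reminder, call and post; the text collects NRT use; status still missing; coded as smoking; non-abstinent in all four outcomes that need Day 28 status. The trigger can be read as either item missing or both missing. The gap is the same for a woman without smoking status on either reading.

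**The plan's own figure.** The sample size concerns the primary outcome and is not in dispute. It is reproduced here because its rates are used below. With p1 = 0.10, p2 = 0.16, mean 0.13, two-sided 5%, 90% power and 1:1 allocation assumed:

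n per arm = [1.960 × √(2 × 0.13 × 0.87) + 1.282 × √(0.10 × 0.90 + 0.16 × 0.84)]² / 0.06² = 659 after rounding up, or 1318 in total. With 660 per arm, power is 90.1%. This agrees with the stated 1320 and 90%.

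**Illustration of size.** The article gives neither Day 28 abstinence rates nor the share of women reached by this text alone. Three assumptions are therefore needed:

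1. True Day 28 abstinence equals the planned late-pregnancy rates of 10% and 16%.
2. A share f of each arm answers this text and no other Day 28 contact.
3. These women are abstinent as often as the rest of their arm.

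Abstinent women miscoded = 660 × (0.10 + 0.16) × f = 171.6 × f. Observed rates are 0.10 × (1 − f) and 0.16 × (1 − f). The risk ratio therefore stays at 1.6, while the risk difference shrinks to 6.0 × (1 − f) points.

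| f | Miscoded of 1320 | Risk difference (points) | Power, 660 per arm |
|---|---|---|---|
| 0 | 0 | 6.0 | 90% |
| 5% | 8.6 | 5.7 | 88% |
| 10% | 17.2 | 5.4 | 86% |
| 20% | 34.3 | 4.8 | 82% |

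If the women reached by text are abstinent only half as often as the others, the counts halve to 4.3, 8.6 and 17.2.

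**Unequal shares.** With 10% in control and 5% in the intervention arm, the observed rates are 0.10 × 0.90 = 9.0% and 0.16 × 0.95 = 15.2%, a risk ratio of 1.69. With 5% and 10%, they are 9.5% and 14.4%, a risk ratio of 1.52. Nothing in the article says whether the shares differ, or in which direction.

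**The case against.** The strongest objection is that a journal article condenses the full protocol. It describes the text as being about NRT use, but does not reproduce the message or say that nothing else is asked. A reader might infer it as established that the text leaves smoking out. The article does not support that certainty, since the script is not shown and a shortened description is possible. What stands is that the article names missing smoking status as a trigger and, for the 36-week text, does state the smoking content. If the Day 28 text does ask about smoking, the description needs correcting.

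Second, the affected group is a residue. It consists of women who gave no status through the app, the online questionnaire, the reminder, the call or the posted form, and who nevertheless answer a later text. This is right, and it limits the size. It does not remove the point, because these are the women the text exists to reach.

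Third, the sensitivity analyses vary the missing-equals-smoking assumption. They show how far results depend on it, but cannot recover an answer that was not requested.

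Fourth, a reader might infer that the miscoding biases the comparison between arms, because participants know their allocation and the intervention arm receives tailored texts. The article gives no evidence of differential response. App prompts and appointment reminders are not described as limited to one arm, and researchers who collect data are blinded. Differential misclassification is possible, but not shown.

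**Conclusion.** The point holds as a correctable gap in the described Day 28 data collection. On the article's wording, a woman without Day 28 smoking status who answers the last-resort text remains without it, and the main analysis counts her as smoking in four secondary outcomes.

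The primary outcome, its sample size and its power are unaffected. That outcome uses late-pregnancy status, for which the text asks about smoking and NHS records add a further source.

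The number of women affected is not given and may be small. The 9 to 34 in the illustration depends wholly on the assumed 5% to 20% share and on borrowing the late-pregnancy rates for Day 28. A reader might carry those counts straight over to women with validated late abstinence who fail the combined outcome. That would require Day 28 non-response to be unrelated to later response. Women engaged enough to report abstinence and supply a sample late in pregnancy probably answered at Day 28 more often, so the counts would probably be too high for them.

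**What to change.** Add smoking in the past 24 hours and the past 7 days to the Day 28 direct-reply text, and state that the reply counts as Day 28 smoking status. If the text already asks this, correct the description under Day 28 after the QD and say that the reply is used.

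No change is needed to the sample size, the primary outcome or the analysis model. There are two costs. A slightly longer text may marginally lower replies to the NRT question. Also, recruitment began in June 2021, so a change now means that Day 28 status is ascertained differently for participants before and after it. The date of the change should be reported. Because women are randomised concurrently to both arms, the change in method falls on the arms in a balanced way.

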##### Pilot phase only

Participants were asked to re-complete the NRT concerns and necessity belief measures they first completed at baseline.^29^

#### 36 weeks of gestation or delivery (if earlier)

We will ask participants about smoking, adherence to NRT since 28-day follow-up and use of NHS stop smoking support. We will send non-responders a direct-reply text message asking about smoking in the previous 7 days.

#### Routine data collected from medical records

NHS hospitals collect smoking status and exhaled CO from every woman from week 36 of gestation onwards, and we will collect these data from NHS records. We will also extract maternal and fetal pregnancy outcome data from medical records. In NHS hospitals, research staff will collect these data; otherwise, the research team contact relevant NHS staff to ask for this information. Where birth outcome data cannot be obtained from records, using methods outlined above, we will ask participants to provide birth weight, gestation at delivery, whether they underwent caesarean section or the baby was admitted to special care or had any congenital abnormality and whether they were a smoker or non-smoker at delivery.

#### Validation of smoking abstinence

For participants who report 7-day smoking abstinence at 36 weeks or later, we will collect saliva samples as they attend hospital, at home visits or postally (see above). Before giving samples, participants will be asked about any recent smoking, vaping or NRT use.

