**Methods and analysis:**

A two-arm parallel-group RCT was conducted for pregnant women aged ≥16 years and who smoke ≥1 daily cigarette (pre-pregnancy smoked ≥5) and who agree to use NRT in an attempt to quit. Recruitment is from antenatal care settings and via social media adverts. Participants are randomised using blocked randomisation with varying block sizes, stratified by gestational age (<14 or ≥14 weeks) to receive: (1) usual care (UC) for stop smoking support or (2) UC plus an intervention to increase adherence to NRT, called ‘Baby, Me and NRT’ (BMN), comprising adherence counselling, automated tailored text messages, a leaflet and website. The primary outcome is biochemically validated smoking abstinence at or around childbirth, measured from 36 weeks gestation. Secondary outcomes include NRT adherence, other smoking measures and birth outcomes. Questionnaires collect follow-up data augmented by medical record information. We anticipate quit rates of 10% and 16% in the control and intervention groups, respectively (risk ratio=1.6). By recruiting 1320 participants, the trial should have 90% power (alpha=5%) to detect this intervention effect. An economic analysis will use the Economics of Smoking in Pregnancy model to determine cost-effectiveness.

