### Objectives

#### Primary objective

To determine whether, when added to the usual NHS cessation support, the BMN intervention increases smoking abstinence during pregnancy, as measured in late pregnancy or at childbirth, with exhaled CO and/or saliva samples used to validate self-reported abstinence.

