### Data collection

Table 1 shows all participant data collection at time points outlined below and indicates how intervention delivery fits with this. Figure 1 is a study flow diagram. We indicate which measures will be used for research purposes in the pilot only.

**Table 1 T1:** Schedule of data collection and intervention delivery time points

Data collected	Time point								
	Pre-baseline (consent)	Baseline*	Pre-Quit Date	Days 1–3	Day 7	Day 14	Day 21	Day 28	Delivery (Week 36 gestation)
Informed consent	X†								
Smoking status/ CPD/use of ecigs		X			P‡			X	X
Cravings & tobacco withdrawal		P			P			P	
NRT concerns & necessity beliefs		P						P	
Saliva samples		P			P				X
Exhaled CO		X							X
NRT adherence data					P			X	X
Reported engagement with intervention								X	
NicUse app data collection									
Medical records data									X
Intervention Delivery (both trial arms)									
Counselling from SSPs offered			X	X	X	X	X	X	
NRT dispatch			X		X	X	X	X	

*Randomisation follows baseline data collection

†X=data collected in both pilot and full trial phase

‡P=data collected only in the pilot phase

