### Outcomes

#### Primary outcome

Reported smoking abstinence in late pregnancy or around childbirth with appropriate biochemical validation.

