#### Assessment of efficacy

The primary efficacy endpoint is reported abstinence in late pregnancy or around childbirth, validated by appropriate biochemical measures (binary—abstinent or non-abstinent). The primary analysis model will include all randomised participants as part of the groups to which they were allocated, with any missing primary endpoints imputed as being non-abstinent. We will compare abstinence between treatment groups using logistic regression, with fixed effects of the treatment group, gestation at baseline (the stratification factor) and other predictive baseline covariates (pre-specified in the SAP). In addition to the point and interval estimate of the OR for allocation, we will use the fitted model to obtain estimates of treatment effects on both the relative risk and risk difference scales. Binary secondary outcomes (eg, other abstinence outcomes) will be analysed in a broadly similar manner to the analysis of the primary outcome. Secondary outcomes including adherence to NRT, NRT adherence intensity, cotinine (smoking exposure), necessities/concerns and birth outcomes will be compared between arms using appropriate generalised linear models. All other outcomes will be summarised descriptively by a randomised arm. If the relevant data are sufficiently complete, we will perform exploratory analyses to decompose the total effect of allocation on the primary outcome into indirect effects (ie, those mediated by improved NRT adherence/usage) and direct effects (ie, those not mediated by improved NRT adherence/usage).

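### Biochemical validation is described only from 36 weeks, while final follow-up may fall at an earlier delivery, leaving abstainers who deliver before 36 weeks no described route to a validated primary outcome

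*Protocol article*

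**What the plan says.** All references are to the protocol article.

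**Timing of follow-up and outcome**
- The final smoking follow-up has the heading "36 weeks of gestation or delivery (if earlier"), so births before 36 weeks are foreseen and smoking status is requested from those women.
- The Primary objective sets no gestational floor. Abstinence is assessed "as measured in late pregnancy or at childbirth, with exhaled CO and/or saliva samples used to validate self-reported abstinence".
- The Primary outcome section also sets none: "Reported smoking abstinence in late pregnancy or around childbirth with appropriate biochemical validation".
- The Abstract does set one: "The primary outcome is biochemically validated smoking abstinence at or around childbirth, measured from 36 weeks gestation".

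**Validation**
- Saliva (Validation of smoking abstinence): "For participants who report 7-day smoking abstinence at 36 weeks or later, we will collect saliva samples". Samples may be taken at hospital, at a home visit or by post.
- Exhaled CO (Routine data collected from medical records): "NHS hospitals collect smoking status and exhaled CO from every woman from week 36 of gestation onwards".
- Table 1 places saliva, CO and smoking status in one column, headed "Delivery (Week 36 gestation").

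**Analysis**
- Assessment of efficacy analyses all randomised women, "with any missing primary endpoints imputed as being non-abstinent".
- Procedures for missing, unused and spurious data plans sensitivity analyses that impute under several missing-at-random and missing-not-at-random scenarios.

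**The concern.** The follow-up schedule and the validation rules do not cover the same women. Someone who delivers at, say, 34 weeks is asked whether she smokes, but neither described source of biochemical evidence applies to her. The primary endpoint requires validation, so her reported abstinence can fail in either of two ways: as unvalidated, or as missing and then imputed as smoking.

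True successes would be lost from the primary outcome, which shrinks the absolute difference and costs some power. Timing of birth is also not incidental in this trial. The Introduction links stopping smoking to fewer premature births, and gestational age at birth is itself listed under Other outcomes. The gap lies in sample collection, so an analysis plan written later cannot recover a sample that was never taken.

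**Working it through.** **1. Passages side by side, for a woman who delivers before 36 weeks and reports abstinence**

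| Element | Section | Covers her? |
|---|---|---|
| Smoking questionnaire | 36 weeks of gestation or delivery (if earlier) | Yes |
| Outcome definition | Primary objective; Primary outcome | Yes, no floor stated |
| Outcome definition | Abstract | Not on a literal reading |
| Saliva sample | Validation of smoking abstinence | Not on a literal reading |
| Routine CO | Routine data collected from medical records | Not described |
| Saliva and CO column | Table 1 | Unclear: the heading names both delivery and week 36 |
| Classification if missing | Assessment of efficacy | Non-abstinent |

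No section says how she is validated or classified.

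**2. The plan's own sample size**

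Inputs from Full trial sample size estimate: 10% control; 16% intervention (10% plus 6 points); two-sided 5%; 90% power; N = 1320. I assume 1:1 allocation (660 per arm), since the article gives no ratio.

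With p̄ = 0.13, the pooled-variance formula without continuity correction is

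n = {[1.960·√(2p̄(1−p̄)) + 1.282·√(p₁(1−p₁) + p₂(1−p₂))] / (p₂ − p₁)}²

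= {[1.960·√0.2262 + 1.282·√(0.0900 + 0.1344)] / 0.06}²

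= {[0.932 + 0.607] / 0.06}², which gives 659 per arm, or 1318 in total.

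The stated 1320 is reproduced. Power at 660 per arm is

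Φ{[0.06·√660 − 0.932] / 0.474} = Φ(1.286) = 90.1%.

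**3. Effect of losing early-delivery quitters**

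Let f be the share of true quitters who deliver before 36 weeks. The documents give no value, so 2% to 10% is an assumed range. If all of them are scored as smokers and f is equal by arm, the rates become 10%(1 − f) and 16%(1 − f). The risk ratio stays at 1.60 because (1 − f) cancels. Quitters lost are 660 × 0.10 × f and 660 × 0.16 × f.

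| f | Control | Intervention | Risk difference (points) | Power | Quitters lost (control / intervention) |
|---|---|---|---|---|---|
| 0% | 10.0% | 16.0% | 6.0 | 90.1% | 0 / 0 |
| 2% | 9.8% | 15.7% | 5.9 | 89.4% | 1.3 / 2.1 |
| 3% | 9.7% | 15.5% | 5.8 | 89.1% | 2.0 / 3.2 |
| 5% | 9.5% | 15.2% | 5.7 | 88.3% | 3.3 / 5.3 |
| 8% | 9.2% | 14.7% | 5.5 | 87.2% | 5.3 / 8.4 |
| 10% | 9.0% | 14.4% | 5.4 | 86.3% | 6.6 / 10.6 |

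**4. Unequal shares by arm (also assumed)**
- Control 5%, intervention 3%: 9.5% v 15.5%, risk ratio 1.63, power 91.2%.
- Control 3%, intervention 5%: 9.7% v 15.2%, risk ratio 1.57, power 85.8%.

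The risk ratio moves by about 0.03 in either direction.

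**The case against.** **The lenient reading.** The reference to 36 weeks in the saliva rule may be shorthand for the follow-up time point, which includes earlier delivery. The objective, the outcome definition and Table 1 are all compatible with a sample at or after an early birth, and the hospital, home and postal routes do not require the woman to be still pregnant. This part stands. A reader might infer that early deliverers are automatically counted as smokers, but no section states that rule. It follows only when the narrow saliva and CO wording is combined with the missing-data rule. The lenient reading does not remove the mismatch, however: the follow-up heading includes earlier delivery, the saliva rule leaves it out, and the Abstract repeats the 36-week floor.

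**A condensed article.** The full protocol and analysis plan may settle classification. That is fair for detail the article merely omits. Here the point is a conflict between rules the article does state, and it concerns sample collection.

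**Existing safeguards.** Counting missing as smoking is a declared convention, and sensitivity analyses to it are planned. A secondary outcome also reports abstinence at both 28 days and late pregnancy without validation. These help in part. The missing-data section speaks of missing smoking status, whereas these women have reported status and lack only validation, so it is unclear whether they are included.

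**Size.** Only true abstainers can be misclassified. The Introduction's link between stopping and fewer premature births suggests their early-delivery share is lower than that of the trial as a whole, so the upper end of the range has no support in the article. The 10% planning rate comes from similar studies and may already reflect such losses, in which case the power figures deduct them twice. Both points stand, and they make this a modest issue.

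**Conclusion.** The mismatch is real. Follow-up, objective and outcome definition reach women who deliver before 36 weeks; the described validation does not. On a literal reading, a reported abstainer among them cannot become a validated success.

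Under an assumed 2% to 10% share of quitters, equal by arm and all scored as smokers, the loss is 0.1 to 0.6 points of risk difference and about 1 to 4 points of power. Power falls below the promised 90% even at 2%, but only because the design starts at 90.1%. The documents do not support a claim that the relative effect is biased: with equal shares the risk ratio is unchanged, and with modestly unequal shares it moves slightly in either direction.

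Severity is minor to moderate. It is worth correcting because it touches the primary endpoint and the remedy is cheap, not because it threatens the trial's conclusion.

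**What to change.** 1. Reconcile the Abstract, the Primary outcome section, the final follow-up section, the routine-data section and Validation of smoking abstinence on one window: *from 36 weeks, or at delivery if earlier*.
2. Change the saliva trigger to *7-day abstinence reported at 36 weeks, or at delivery if earlier*. Collect the sample at that report through the existing hospital, home or postal routes, and use any CO reading recorded around that delivery.
3. State how a woman who delivers before 36 weeks is classified in the primary outcome, with and without a sample.
4. Name self-reported abstainers with an unvalidated early delivery explicitly in the planned missing-at-random and missing-not-at-random sensitivity analyses.

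Do not add an analysis that excludes early deliveries. It would condition on an event after randomisation that the intervention could affect, and it would depart from the all-randomised analysis.

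The cost is a wording change and a few extra kits. Follow-up is planned to October 2026, so the change can help only women whose samples are not yet due; item 4 covers those whose sampling opportunity has already passed.
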